##### Power for Hypothesis 1a

We have considerable *power* to detect relatively small correlations for secondary analyses. As a preliminary power estimate, if we assume a normal distribution and α=.05, we have 80% power to detect a correlation coefficient as small as 0.2 with 200 patients. For larger, more meaningful correlations, we have well over 90% power starting at a sample of 375.

#### Aim 2: Behavioral Processes

##### Hypothesis 2a

Adapt2Quit participants will have higher scores on the PCS than control participants. To analyze hypothesis 2a, we will first create a generalized linear model where the dependent variable is the averaged PCS score during follow-up (see the section Hypothesis 1a), the independent variable is randomization group, and the baseline PCS score is included as a covariate. Furthermore, to fully use the repeated measures of the PCS, we will develop a random effects interrupted time series model evaluating the change in slope of PCS over time, comparing the Adapt2Quit intervention and comparison group. This will be implemented using a segmented regression to evaluate changes in slope early in the intervention and sustain change over time in the latter months of the 6-month follow-up.

##### Power for Hypothesis 2a

In a prior smoking cessation study, the mean (SD) of PCS was 4.79 (1.96) [23]. On the basis of these results, for power calculations, we assumed a meaningful difference in the averaged PCS score to be equal to 1 SD, assumed the mean in control to be 4.79, and set α at .05. To detect a difference of 1 SD, we have 99% power with a sample of 120 participants per group, further demonstrating power for aims 1 and 2.

##### Hypothesis 2b

Adapt2Quit participants will adopt more cessation-supporting actions (quitline and NRT) than control participants. For hypothesis 2b, the independent variable is again the randomization group. Each dependent variable will be modeled separately. There are several ways to analyze quitline use, including time to first call completed (time from baseline when the first call with the counselor was conducted in a number of weeks) or whether the participant used the quitline and the number of contacts between the patient and counselor. We chose the time to first call completed with the quitline counselor because it matters how quickly the intervention succeeded in motivating participants to call the quitline (if the call happened in the first few days of the intervention or later). The participant may initiate the call, or the counselor can call the participant following a texting referral.

##### Power for Hypothesis 2b

Analysis and the power calculation for time to first call completed is similar to the hypothesis 3b analysis. The use of NRT will be assessed via self-report at the 6-month follow-up. To analyze NRT use, a dichotomous variable, we will create a logistic model with the use of NRT (yes or no) as the dependent variable and randomization as the independent variable.

#### Aim 3: Effectiveness

##### Hypothesis 3a: Primary Outcome

Adapt2Quit participants will have greater smoking cessation rates (6-month point-prevalence biochemically verified) than control participants. For our primary outcome, we will follow recommendations from the Society for Nicotine and Tobacco Research and other experts. While we will attempt to minimize dropout rates loss to follow-up (missing outcomes) in trials such as ours cannot be fully averted [41]. Penalized imputation (missing=still smoking) is not a conservative approach and can be biased (against a group), especially when there is a differential missing between the groups [41]. Thus, the recommended approach is to use inverse probability weighting [42]. In this approach, the first step is to develop a logistic regression model to predict nonmissingness using variables that are found to be different between study participants with and without missing data. The next step is to calculate the inverse probability of nonmissingness and use it as the weight in a logistic regression model to compare the cessation rate between two study groups [43]. Along with inverse probability weighting, we will present penalized imputation and a complete case analysis (limited to those with complete data) as sensitivity analyses. We propose to biochemically verify participants who self-report quitting smoking using a CO meter.

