### Recruitment

Recruitment was spread over the 3.5 years of the study. Study participants were recruited at urban and rural health care settings across 3 health care systems in the United States (UMass Memorial Medical Center, Baystate Health, and Johns Hopkins University). We used an opt-out recruitment strategy, with some variations between the three sites. At all 3 sites, after obtaining a Health Insurance Portability and Accountability Act waiver, potential participants who met our inclusion criteria in the clinical data warehouse were identified. At the UMass Chan and Baystate Medical Center, an initial invitation letter with a self-addressed, stamped opt-out postcard was sent to those eligible from the local site principal investigator outlining the study’s purpose. Johns Hopkins University’s site used emailed study invitation letters with instructions to opt-out via email instead of or in addition to mailed letters and “opt-out” postcards for those without an email address. Instructions were provided on how to opt-out by email. At all sites, individuals who opted out or whose email was returned undelivered within 2 weeks were removed from the recruitment list.

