### Randomization

Separate randomization tables were created for each site to enhance the balance between the two groups. Participant allocation to study arms was based on a permuted block scheme in which treatment assignments were made within blocks so that numbers assigned to each treatment arm are equal after a block has been filled. Blocks of various sizes (2, 4, and 6) were used in random order to facilitate allocation concealment. As in our prior technology-based trials, we embedded randomization within the technology [29,30]. After completing the screening, informed consent, and baseline data collection, the research staff entered the participant ID and participant mobile phone number from the survey into a web-based system, which then assigned the allocation based on the randomization table. Using this technique, participants and staff were blinded to allocation during the initial session. The research staff were subsequently unblinded to provide personalized training for the intervention and control groups, as noted.

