### Data Analysis

#### Statistical Analysis and Power Calculations

To preserve randomization, all primary analyses will be on an intent-to-treat basis. Secondary analyses will explore dose-response effects among those with variable levels of adherence to the intervention. All analyses will be 2-sided, and the α error level will be set at .05. We will begin by examining univariate statistics (means, medians, SDs, frequencies, percentages, and 95% CIs) and distributions of the variable of interest. We will examine the balance of participant characteristics by study groups and account for any imbalances in our multivariable analysis. To address sex as a biological variable, we will stratify the analyses by male and female to evaluate whether the mechanisms and outcomes are modified by sex. We will test group differences either using chi-square tests of independence (categorical variables), *Z* test, or a 2-tailed *t* test (continuous variables), or the equivalent nonparametric tests depending on the distribution of the variables. Baseline differences between the intervention and control group will be established based on standardized differences, rather than on tests of statistical significance.

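### Randomisation is stratified by site, but the primary model is described with study group only, and the one general covariate rule follows observed imbalance rather than site or prognosis

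*Protocol article*

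**What the plan says.** **Allocation.** Under Randomization: "Separate randomization tables were created for each site to enhance the balance between the two groups". Permuted blocks of 2, 4 and 6 were used so that "numbers assigned to each treatment arm are equal after a block has been filled". Recruitment ran "across 3 health care systems in the United States". Site is therefore a stratification factor with three levels.

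**Primary analysis.** Under Hypothesis 3a, a logistic model for non-missingness is built "using variables that are found to be different between study participants with and without missing data". Its inverse probability is then the weight, and the plan is to "use it as the weight in a logistic regression model to compare the cessation rate between two study groups". Study group is the only term mentioned.

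**Covariates in general.** Under Statistical Analysis and Power Calculations: "We will examine the balance of participant characteristics by study groups and account for any imbalances in our multivariable analysis". On how imbalance is judged: "Baseline differences between the intervention and control group will be established based on standardized differences, rather than on tests of statistical significance". No threshold is given, and the multivariable analysis is not identified as the primary model or as a secondary one.

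**Elsewhere.** Where the authors intend a specific covariate they name it. For H2a, "the baseline PCS score is included as a covariate". The H2b model for nicotine replacement names randomisation only. No model in the article names site.

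**The concern.** An analysis should normally reflect the way participants were allocated. When site affects the outcome and the arms are balanced within site, an arm-only analysis counts between-site variation as noise, although the design has already removed it from the treatment comparison.

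The imbalance rule does not repair this. It selects on the difference between arms, and a stratification factor shows almost none. It also passes over strong predictors of quitting that happen to be balanced, and it brings in weak predictors that differ by chance.

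A second issue is when the choice is made. If the rule applies to the primary model, the covariates are settled only after the baseline table has been seen by arm, without a fixed threshold. In logistic regression that choice also changes what is estimated, because adjusted and unadjusted odds ratios are different quantities. At stake are a little power and, more importantly, a primary estimate that is not fully fixed in advance.

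**Working it through.** **1. Can the imbalance rule select site?** With a largest block of 6, the arms at one site can differ by at most 3 people among those randomised. Take 757 participants, about 378.5 per arm, and assume a small site of 50, since site sizes are not given in the text. The worst split is 26.5 against 23.5.

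- Proportions: 26.5/378.5 = 0.0700 and 23.5/378.5 = 0.0621, a difference of 0.0079.
- SD at the mean proportion 0.066: √(0.066 × 0.934) = 0.248.
- Standardised difference: 0.0079/0.248 ≈ 0.03, and smaller for larger sites.

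That is close to no difference, so the rule would hardly ever select site.

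**2. How much outcome variance could site explain?** The article gives no quit rates by site, so all site rates here are assumptions. For three equal sites, R² = (variance of site rates) / (p̄(1 − p̄)).

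- 6/10/16%: 0.00169/0.0953 = 0.018.
- 5/10/20%: 0.00389/0.1031 = 0.038.
- 2/5/17%: 0.0042/0.0736 = 0.057.

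**3. Expected effect on the arm-only test.** With arms balanced within site and no treatment effect, the true standard error is about √(1 − R²) times the one the arm-only model reports. At 2/5/17% this is √0.943 = 0.971. The effective critical value becomes 1.960/0.971 = 2.018, and the two-sided error about 4.4%. So the test is slightly conservative.

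**4. Simulation.** Unweighted logistic regression, 600 participants, three equal sites, arms exactly balanced within site, a 7-point average effect under the alternative, and 4,000 runs per scenario. The control rates average 8%, the middle of the article's planning range of 7% to 9%.

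| Assumed control rates by site | Type I error, arm only | Type I error, with site | Power, arm only | Power, with site |
|---|---|---|---|---|
| 8/8/8% | 4.7% | 4.7% | 76.8% | 76.9% |
| 5/8/11% | 4.3% | 4.5% | 77.6% | 78.2% |
| 3/8/13% | 4.4% | 5.1% | 76.9% | 77.9% |
| 2/5/17% | 4.1% | 4.9% | 78.3% | 81.1% |

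The Monte Carlo standard error is √(0.05 × 0.95/4000) ≈ 0.3 points for type I error and √(0.77 × 0.23/4000) ≈ 0.7 points for power. Adding site gains 0.1, 0.6, 1.0 and 2.8 points of power.

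**5. How many covariates can the model carry?** With 300 per arm and the planned 7-point difference:

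- Control 7%: 300 × 0.07 + 300 × 0.14 = 21 + 42 = 63 quits.
- Control 9%: 300 × 0.09 + 300 × 0.16 = 27 + 48 = 75 quits.

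Arm and two site terms take three parameters beyond the intercept. Only a few more are prudent.

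**The case against.** The strongest reply is that the article is silent on site rather than excluding it. The Hypothesis 3a paragraph outlines a weighting method in a few sentences, and a full covariate list is commonly left to an analysis plan that is not shown here. That stands as far as it goes: silence about site would not be a finding by itself. But the imbalance rule is stated positively. The Paper Objective says the article describes the analyses of the primary and secondary hypotheses, and Conclusions and Future Work says the results papers will follow the plans given here.

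Other objections stand and limit the point:

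- A reader might infer that the primary model is both arm-only and chosen from the baseline table. The text does not support both at once. Hypothesis 3a taken alone gives an arm-only model; if the general rule governs, the model is not arm-only. The article does not say which applies.
- A reader might infer that the rule excludes site with certainty. Balance is guaranteed among those randomised, not among those with outcomes (591 of 757 had completed follow-up as of May 2024). Site could also enter through the non-missingness model.
- A reader might infer that omitting site invalidates the test or that adjusting shrinks the standard error of the log odds ratio. Neither holds. The error is on the conservative side. In a check with no treatment effect at assumed rates of 6/10/16%, the mean standard error rose from 0.267 to 0.270 when site was added. Any power gain comes from the conditional log odds ratio lying further from zero.
- The prognostic case for site is plausible but not demonstrated. Referrals go to the Massachusetts and Maryland quitlines, and one of the three sites used emailed invitations, but the article reports no outcomes by site.

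**Conclusion.** The point holds in a limited form. The stratification factor is absent from the primary model as described. The only general covariate rule would hardly ever select it, takes no account of prognosis, and has no stated threshold or stated link to the primary analysis.

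The statistical cost of omitting site is small: no type I inflation, a slightly conservative test, and about 0 to 3 points of power. The upper end is reached only with a wide assumed spread of 2/5/17%. These figures rest on assumed site rates, three equal sites, exact balance within site and unweighted models. The more important weakness is that the article does not settle whether the primary estimate is unadjusted or adjusted for whatever proves imbalanced. This is an improvement that should be made, not a threat to the trial's validity.

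**What to change.** Before any unblinded analysis:

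1. Set the primary weighted model as CO-verified cessation on arm, site (3 levels) and a very short fixed list of baseline predictors already collected, for example time to first cigarette and having stopped for at least one day in the past year. Keep the list this short because of the 63 to 75 quits expected.
2. State that the resulting odds ratio is conditional on these covariates, or report a standardised risk difference alongside it.
3. Include site in the H2a and H2b models.
4. Use standardised differences for description, and limit imbalance-driven adjustment to a sensitivity analysis.

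The cost is a change of analysis wording. No new data are needed. The price in the model is a few extra parameters and a primary odds ratio that is conditional rather than marginal.

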##### Power for Primary Outcome (Hypothesis 3a)

In our prior National Cancer Institute trial, we observed an absolute 9% difference in the standard messaging versus no-messaging control group [29]. We expect socioeconomically disadvantaged groups to have lower cessation rates than non–socioeconomically disadvantaged groups. Thus, we calculated power using a range of control cessation rates from 7% to 9%. We started at 7%, because it is the estimated rate at which the general population of all individuals who smoke quit without any intervention [34]. On the basis of the recommender enhancements (and further pilot data), we saw an additional marginal difference of 6% at 30 days (even higher for African American individuals who smoke) and expect this difference to continue and expand over time as the recommender system continues to learn and adapt to the individual; however, to be conservative and recognizing the potential difficulty in impacting behavior in this population, we chose to power for a small difference, namely 7%. Although our hypothesis is directional, we have chosen to adopt the commonly used conservative approach of 2-sided tests for all our power calculations. On the basis of a 2-sided chi-square test of equal proportions, α=.05, for all these base rates, we will have 80% power with 600 participants (N=300 per arm). Considering loss to follow-up, we plan to oversample by 25% and thus have budgeted for a total of 750 participants to complete baseline and be randomized. On the basis of our prior experience recruiting from clinical systems, we expect the dropout rate to be lower than the 25% we have assumed in our calculations.

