### Comparison

To isolate the effect of the Adapt2Quit recommender system, comparison participants do not receive tailored motivational messages but receive the texting quitline facilitation and the texting assessment of smoking status with the same frequency as intervention participants.

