Our study will provide important evidence on whether a more personalized approach using machine learning can encourage quitline use and support smoking cessation, compared to a text-based referral to quitline. In previous papers, we described our pilot studies testing the Adapt2Quit intervention [16,35,54]. Furthermore, our prior large randomized controlled trial compared the Adapt2Quit intervention to a system that delivered messages based on participants’ baseline readiness to quit [17]. In that trial, we recruited participants online as well as through referrals from friends and family. In addition, messages were delivered by email rather than by text, as is being done in this trial. The previous study also did not include biochemical verification of smoking cessation. Beyond the potential benefit of computer-tailored messaging, our system aims to actively engage participants with the quitline. Quitlines have proven to be effective in supporting people to quit smoking, yet using a quitline and attending counseling sessions is a significant step for individuals from socioeconomically disadvantaged backgrounds who smoke. Currently, only 2% to 3% of people who smoke use the quitline, with usage rates even lower among individuals from socioeconomically disadvantaged backgrounds [34]. Prior research has shown that it is possible to use a low-intensity intervention such as texting to increase motivation and the use of cessation resources among people who smoke [55].

In addition to our system, one group compared a similar recommender system in a pilot trial to a system that selected messages based on a knowledge base. They compared the message appreciation, engagement with the system, and one’s own self-reported smoking cessation status (7-day point prevalence) [18]. Another group developed a recommender system for smoking cessation and promoting physical activity [56]. This group described an experiment they conducted to identify the optimal approach for selecting messages. In addition, a systematic review examined the potential of using another machine learning approach—reinforcement learning—for similar purposes [57]. Together, these approaches highlight the potential of the use of machine learning approaches to enhance a widely used behavioral intervention: computer-tailored health communication.

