### Strengths and Limitations

We describe the protocol for a rigorous evaluation of behavioral intervention among individuals from socioeconomically disadvantaged backgrounds. Since recruitment for our study is complete, we also present participant characteristics. Using an opt-out recruitment strategy across 3 different health care systems, we successfully recruited a diverse sample, which has been challenging to achieve for clinical trials. Our fully remote procedures for screening, baseline, and follow-up may have reduced barriers to recruitment. Notably, 35% (265/757) of our sample identified as Black and 16% (121/757) as Hispanic or Latino. This more representative sample suggests that our study findings will be more generalizable to the US population. One limitation is that our participants reported higher motivation levels for quitting smoking than the general population, which is likely due to the recruitment strategy attracting those who were more motivated to participate in a tobacco cessation study. Because we only used insurance status to determine socioeconomically disadvantaged, some participants may not align with all characteristics that may describe socioeconomically disadvantaged.

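### The stated 80% power holds only at or below a 7% control rate that the plan describes as quitting without intervention; at 8% and 9%, inside its own range, power is 76.8% and 73.8%

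*Protocol article*

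**What the plan says.** The sample size is justified in the protocol article under Power for Primary Outcome (Hypothesis 3a).

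- **Control rate.** The authors write that "we calculated power using a range of control cessation rates from 7% to 9" percent. The lower end is explained as follows: "We started at 7%, because it is the estimated rate at which the general population of all individuals who smoke quit without any intervention". They also expect disadvantaged groups to quit less often than others.
- **Effect.** They report that "we observed an absolute 9% difference in the standard messaging versus no-messaging control group" in an earlier trial, and a further 6 points for the recommender at 30 days. They then choose an absolute difference of 7 points and call that choice conservative.
- **Test and claim.** "On the basis of a 2-sided chi-square test of equal proportions, α=.05", and then: "for all these base rates, we will have 80% power with 600 participants (N=300 per arm").

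The control arm is described under Comparison: "comparison participants do not receive tailored motivational messages but receive the texting quitline facilitation and the texting assessment of smoking status". Flow of the Intervention explains the facilitation. Participants in both arms are asked by text every 14 days whether they want quitline referral, until they say yes. Study staff refer those who accept, and the quitline then calls them and provides counseling.

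The Discussion states that "Quitlines have proven to be effective in supporting people to quit smoking" (Principal Findings) and that "our participants reported higher motivation levels for quitting smoking than the general population" (Strengths and Limitations). The power paragraph does not mention the facilitation.

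**The concern.** The lower end of the control range is a rate for people who receive nothing, and the trial's controls receive an active referral service. The article regards that service as effective. In its Introduction it expects texting to raise quitline use and, through that, cessation. A reader therefore cannot tell whether the 7% to 9% range describes the control arm that was actually run.

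This matters because the plan fixes an absolute difference. In this range of rates the binomial variance grows with the control rate, so the same 7 points becomes harder to detect. If facilitation moves controls off the 7% anchor, power falls. The paragraph nevertheless assures the reader that 80% holds at every rate considered. That figure will be used to judge how informative a non-significant result is.

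**Working it through.** **Inputs**, all from Power for Primary Outcome (Hypothesis 3a): two-sided α = 0.05, chi-square test of two proportions, n = 300 per arm, absolute difference d = 0.07, control rate p₁ from 0.07 to 0.09. Equal allocation follows from the Randomization section.

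**Formula.** With p₂ = p₁ + d and p̄ = (p₁ + p₂)/2:

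- SE₀ = √[2·p̄(1 − p̄)/n], the pooled standard error under the null
- SE₁ = √{[p₁(1 − p₁) + p₂(1 − p₂)]/n}, the standard error under the alternative
- Power = Φ[(d − 1.960·SE₀)/SE₁]

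**Step 1: the plan's figure at the anchor (7% v 14%).** p̄ = 0.105, SE₀ = 0.02503, SE₁ = 0.02487. Then (0.07 − 0.04906)/0.02487 = 0.842, and Φ(0.842) = 0.800. The required n is 300 per arm. The stated 80% and 300 are reproduced exactly.

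**Step 2: the rest of the plan's range.**

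- 8% v 15%: p̄ = 0.115, SE₀ = 0.02605, SE₁ = 0.02589. (0.07 − 0.05105)/0.02589 = 0.732, so power is 0.768.
- 9% v 16%: p̄ = 0.125, SE₀ = 0.02700, SE₁ = 0.02685. (0.07 − 0.05293)/0.02685 = 0.636, so power is 0.738.

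**Step 3: detectable difference.** Solving the same formula for the d that gives 80% power at n = 300:

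| Control rate | Power for 7 points | Difference detectable with 80% power | n per arm for 80% power at 7 points |
|---|---|---|---|
| 7% | 80.0% | 7.0 points | 300 |
| 8% | 76.8% | 7.3 points | 325 |
| 9% | 73.8% | 7.6 points | 350 |

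**Step 4: could another version of the test rescue the claim?** Using the unpooled variance throughout gives 80.4%, 77.2% and 74.1%. A continuity correction makes matters worse, needing 328, 353 and 378 per arm. A one-sided test would exceed 80% throughout (87.7%, 85.3%, 83.0%), but the plan says two-sided. None of the two-sided variants gives 80% over the whole range.

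**Step 5: outside the plan's range, as sensitivity only.** The documents give no quit rate for a text-facilitated quitline control, so these rates are assumptions. At 10%, power for 7 points is 70.9% and the detectable difference is 7.9 points. At 3%, the 6-month abstinence figure that the Discussion cites for one texting program, power for 7 points is 94%.

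**The case against.** The strongest defence is that the range already has room for facilitation. The authors expect disadvantaged smokers to quit less often than the general population, yet they start at the general-population figure and go up from it. The Discussion puts quitline use at 2% to 3% of smokers, and lower still in disadvantaged groups. The outcome is verified by carbon monoxide. All of this could keep the control rate low. It is a fair argument and it limits what can be claimed about rates above 9%. It does not rescue the 80%: if the range allows for facilitation, 8% and 9% are realistic control rates, and power there is below 80%.

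Three stronger readings are tempting and are not supported.

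- *The effect evidence belongs to a different comparator.* A reader might infer this from the no-messaging control in the cited trial. But both arms here receive facilitation and status texts at the same frequency, so the randomised contrast is still messages against no messages. The 7 points is also a judgement set below the cited 9, not that figure itself. What stays open is whether a 7-point gain carries over on top of facilitation, and the paragraph does not address this.
- *Power is really about 48%.* That comes from setting 9% against 14%: controls are lifted by facilitation while the intervention arm is held where it was. The intervention arm receives the same facilitation.
- *Power is really 60% to 71%.* Those values need control rates of 15% down to 10%, for which the documents have no source. Participants' higher motivation is stated without any quit rate attached.

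The direction of the loss also depends on the effect scale. If the odds ratio implied by 7% v 14% were held constant instead, power would rise with the control rate, to about 90% at 10%. The plan fixes the absolute difference, so its claim has to be judged on that scale.

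Finally, the article already frames the question as messages compared with text-based quitline referral (Comparison; Principal Findings), so the risk of misreading a null result is smaller than it might seem.

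**Conclusion.** The point holds in a limited form. The claim of 80% power for all control rates from 7% to 9% is wrong at 8% and 9%, where power is 76.8% and 73.8%, a shortfall of 3.2 and 6.2 percentage points. This rests only on the plan's own test, sample size, difference and range.

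The 80% is met only at or below the rate that the plan takes from people who receive no intervention. Because controls are actively referred to a service the article considers effective, the upper part of the range cannot be set aside as unlikely, and the paragraph does not say whether it was included for that reason. How far facilitation raises the control rate cannot be determined from the documents. A rate above 9% is possible but not shown, and so is a rate below 7%.

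**What to change.** In the power paragraph, and wherever the power is quoted again:

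1. State that the 7% to 9% range is the assumed quit rate for a control arm receiving text-facilitated quitline referral, and that the 7 points is the gain of recommender messages on top of the facilitation both arms receive.
2. Replace the single 80% with power by control rate: 80.0% at 7%, 76.8% at 8% and 73.8% at 9%, with detectable differences at 80% power of 7.0, 7.3 and 7.6 points.
3. If rates outside 7% to 9% are shown, label them as a sensitivity range without a source in the plan, and show both directions: for example 10% (power 70.9%, detectable difference 7.9 points) and 3% (power 94%).

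Do not enrol more participants: recruitment and follow-up are complete. The change needs no new data and does not alter the analysis. Its only cost is a less favourable power statement.

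### The claim of 80% power at 300 per arm for every control rate from 7% to 9% holds only at 7%; power is 77% at 8% and 74% at 9%

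*Protocol article*

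**What the plan says.** All the inputs stand in one paragraph of the Protocol article, Power for Primary Outcome (Hypothesis 3a):

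- **Control rates:** "we calculated power using a range of control cessation rates from 7% to 9" percent.
- **Difference:** "we chose to power for a small difference, namely 7" percent. The neighbouring sentences speak of absolute and marginal differences, so this is 7 percentage points.
- **Test:** "On the basis of a 2-sided chi-square test of equal proportions, α=.05". The paragraph also says "we have chosen to adopt the commonly used conservative approach of 2-sided tests for all our power calculations".
- **Claim:** "for all these base rates, we will have 80% power with 600 participants (N=300 per arm").
- **Allowance for loss:** "we plan to oversample by 25% and thus have budgeted for a total of 750 participants". The 300 per arm is therefore the number with outcomes, not the number randomized.

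Allocation is 1:1; under Randomization the blocks are built so that "numbers assigned to each treatment arm are equal after a block has been filled".

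**The concern.** The claim covers a range of control rates with a single sample size and a single absolute difference. For proportions below 50%, the variance p(1−p) rises with p. Moving from 7% vs 14% to 9% vs 16% therefore adds noise while the signal stays at 7 points. Power cannot be the same at all three rates, and if 300 per arm gives 80% at 7%, it must give less at 8% and 9%.

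This is the article's only sample-size justification for the primary outcome, and its Conclusions and Future Work section says that the results papers will follow the plans set out here. If the trial is null, readers would credit the stated design with a 20% chance of missing a 7-point effect anywhere in the planning range. At a 9% control rate the chance is about 26%. The error also runs in the favourable direction, in a paragraph that describes its choices as conservative.

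**Working it through.** **Inputs** (all from the Hypothesis 3a power paragraph, with 1:1 allocation from Randomization): p₀ = 0.07, 0.08, 0.09; p₁ = p₀ + 0.07; n = 300 per arm; two-sided α = .05, so z = 1.960; z for 80% power = 0.842.

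**Formulas** (uncorrected chi-square test, variance pooled under the null and unpooled under the alternative), with p̄ = (p₀ + p₁)/2:

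- SE₀ = √[2p̄(1−p̄)/n]
- SE₁ = √{[p₀(1−p₀) + p₁(1−p₁)]/n}
- Power = Φ[(0.07 − 1.960·SE₀)/SE₁]
- n per arm for 80% = {1.960·√[2p̄(1−p̄)] + 0.842·√[p₀(1−p₀) + p₁(1−p₁)]}² / 0.07²

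**The plan's own figure first, 7% vs 14%.** p̄ = 0.105. SE₀ = √(2 × 0.105 × 0.895/300) = 0.02503. SE₁ = √[(0.0651 + 0.1204)/300] = 0.02487. The argument is (0.07 − 1.960 × 0.02503)/0.02487 = 0.842, and Φ(0.842) = 0.800. The required n is 299.9, that is 300 per arm. The stated figure reproduces exactly, which also confirms that the difference is absolute and the test uncorrected.

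**The same calculation across the stated range:**

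| Control vs intervention | SE₀ | SE₁ | Argument of Φ | Power at 300 per arm | n per arm for 80% | Difference detectable with 80% power at 300 per arm |
|---|---|---|---|---|---|---|
| 7% vs 14% | 0.02503 | 0.02487 | 0.842 | 80.0% | 300 | 7.0 points |
| 8% vs 15% | 0.02605 | 0.02589 | 0.732 | 76.8% | 325 | 7.3 points |
| 9% vs 16% | 0.02700 | 0.02685 | 0.636 | 73.8% | 350 | 7.6 points |

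The total needed rises from 600 to 650 and 700.

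**Does another method rescue the claim?** Power at 300 per arm:

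| Method | 7% | 8% | 9% |
|---|---|---|---|
| Unpooled variance, two-sided | 80.4% | 77.2% | 74.1% |
| Arcsine, two-sided | 80.9% | 77.6% | 74.4% |
| Exact enumeration of the Pearson chi-square test, two-sided | 81.0% | 77.6% | 74.5% |
| Continuity-corrected, two-sided | 76.1% | 72.7% | 69.6% |
| One-sided α=.05 | 87.7% | 85.3% | 83.0% |

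Every two-sided version falls more than 2 points short at 8% and more than 5 points short at 9%. Only a one-sided test exceeds 80% throughout, and the paragraph rules that out. The continuity-corrected row is shown for completeness; the plan mentions no correction.

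**The case against.** The best case for the plan has three parts.

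*The error is small and nothing can be done about it now.* The 7% vs 14% design point is correct, the shortfall at the other rates is 3 to 6 points of power, and the detectable difference moves by only 0.3 to 0.6 points. Recruitment is complete at 757, and a null result will be read mainly from its confidence interval. All of this stands, and it limits the consequence to a correction of the text. It does not make the sentence true.

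*The trial randomized more than 600.* If all 375 per arm had outcomes, power would be 88.0%, 85.3% and 82.7%; at 350 per arm it would be 86%, 83% and 80%. Good retention could therefore restore 80% across the range, and the power of the completed trial is not established here. But the sentence is about 300 per arm, and the extra 150 are there to cover loss. The Results section reports 591 six-month interviews as of May 2024, about 296 per arm if evenly split, which gives roughly 79%, 76% and 73%. That was an interim count, so the final number may be higher.

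*The control rate may lie outside the range.* Above it, power for 7 points drops further, to 66% at 12% and 60% at 15%. The article describes its participants as more motivated than the general population, which points that way. Below it, power rises, to 83% at 6% and 87% at 5%. The article expects lower cessation in disadvantaged groups, verifies abstinence by carbon monoxide and cites a texting programme with 3% abstinence at 6 months, which point the other way. These rates are illustrative assumptions, and the finding rests on none of them.

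**Conclusion.** The statement is wrong as written. With the plan's own inputs, 300 per arm gives 80.0% power at a 7% control rate, 76.8% at 8% and 73.8% at 9%. At the top of the stated range, 80% would need 350 per arm, about 17% more than stated (350/300 = 1.17). The conclusion rests on an absolute 7-point difference, a two-sided uncorrected chi-square test, 1:1 allocation and 300 analysable participants per arm, all of which come from the article. It concerns the planned power at that sample size, not the power of the trial as completed. The primary analysis and the data are unaffected.

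**What to change.** Replace the sentence that claims 80% power at all base rates with:

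> With 300 analysable participants per arm, power to detect a 7-point absolute difference (2-sided chi-square test, α=.05) is 80%, 77% and 74% at control rates of 7%, 8% and 9%; 80% power corresponds to differences of 7.0, 7.3 and 7.6 points.

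Use the same figures wherever the main results paper restates the sample-size justification. The cost is one sentence and a slightly less favourable power statement. No extra enrolment and no change to the analysis is proposed.
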